## Abstract

**Background:**

The Memory Support Intervention was developed in response to evidence showing that: (1) patient memory for treatment is poor, (2) poor memory for treatment is associated with poorer adherence and poorer outcome, (3) the impact of memory impairment can be minimized by the use of memory support strategies and (4) improved memory for treatment improves outcome. The aim of this study protocol is to conduct a confirmatory efficacy trial to test whether the Memory Support Intervention improves illness course and functional outcomes. As a “platform” for the next step in investigating this approach, we focus on major depressive disorder (MDD) and cognitive therapy (CT).

**Method/design:**

Adults with MDD (*n* = 178, including 20% for potential attrition) will be randomly allocated to CT + Memory Support or CT-as-usual and will be assessed at baseline, post treatment and at 6 and 12 months’ follow-up (6FU and 12FU). We will compare the effects of CT + Memory Support vs. CT-as-usual to determine if the new intervention improves the course of illness and reduces functional impairment (aim 1). We will determine if patient memory for treatment mediates the relationship between treatment condition and outcome (aim 2). We will evaluate if previously reported poor treatment response subgroups moderate target engagement (aim 3).

**Discussion:**

The Memory Support Intervention has been developed to be “transdiagnostic” (relevant to a broad range of mental disorders) and “pantreatment” (relevant to a broad range of types of treatment). This study protocol describes a “next step” in the treatment development process by testing the Memory Support Intervention for major depressive disorder (MDD) and cognitive therapy (CT). If the results are promising, future directions will test the applicability to other kinds of interventions and disorders and in other settings.

**Trial registration:**

ClinicalTrials.gov, ID: NCT01790919. Registered on 6 October 2016.

**Electronic supplementary material:**

The online version of this article (doi:10.1186/s13063-017-2276-x) contains supplementary material, which is available to authorized users.

## Background

Patients accurately recall only about one third of the recommendations made during a physician visit [1–8] and during a cognitive behavior therapy (CBT) session [9, 10]. In one study, 25% of patients remembered recommendations that were *not* made [1]. Recall is particularly poor for advice for health-behavior change [11]. Perhaps not surprisingly, poor memory for the content of treatment is associated with poor adherence to medical treatments for chronic conditions [12–16], which is known to be associated with worse outcome [17]. Also, poor memory for CBT is associated with poorer outcome [10].

We have offered various explanations for these findings [18]. First, even when memory is functioning optimally, fallibility is possible at initial encoding, storage or retrieval [19]. Second, a CBT treatment session is typically 50 min long, covers complex information, and can elicit negative emotion. Negative emotion is associated with attentional biasing and narrowing, which impacts encoding [20]. Third, the odds are stacked *against* people learning, generalizing and transferring knowledge to new situations; this is known as the transfer of learning problem [21, 22]. Fourth, memory deficits and biases are common across mental disorders [23–27] and memory deficits are associated with poorer memory for treatment [28, 29].

The good news is that the impact of memory impairment can be minimized. Memory encoding and retention can be markedly improved by the use of memory support techniques. This has been demonstrated in medical visits [13, 30], and among older adults [31] as well as for people with memory impairments associated with Alzheimer’s disease, vascular dementia [32] and frontal lobe dysfunction [33].

We developed and tested the Memory Support Intervention, which is designed to improve patient memory *for treatment*. This approach is *not* intended to have a direct effect on improving memory functioning per se. The Memory Support Intervention was distilled from the cognitive science and education literature based on carefully honed criteria [18]. A small underpowered trial has provided preliminary evidence that the intervention exerts a measurable effect on patient memory for treatment and demonstrates a clinical effect [34].

The Memory Support Intervention has been developed to be “transdiagnostic” (relevant to a broad range of mental disorders) and “pantreatment” (relevant to a broad range of types of treatment). However, investigating these possible broader applications seems premature without first establishing efficacy, which is the aim of the study described in this paper. To create a platform for the “next step” in investigating the approach, we will recruit patients who meet diagnostic criteria for major depressive disorder (MDD) and focus on one biopsychosocial intervention—cognitive therapy (CT). If the results are promising, future directions will test the applicability to other kinds of interventions and disorders and in other settings.

Why focus on MDD? First, MDD is prevalent and causes impairment [35, 36]; second, there is a need to improve treatments for MDD because a proportion of patients do not recover and of those who do recover, the majority relapse [37]; third, memory is poor in MDD and is modifiable [38, 39]; fourth, preliminary data suggest that improving memory for treatment in MDD improves outcome [34, 40, 41].

Why focus on CT for MDD? CT for MDD is well articulated and has been widely studied. Meta-analyses confirm CT as a frontline treatment [42, 43]. Despite these impressive outcomes, there is room for improvement [44, 45].

This study protocol addresses two additional considerations. First, older age, lower intelligence and chronic depression each predict poorer response to treatment for depression, including CT [46]. Impairment in declarative memory is also associated with poorer outcome [47–50]. Moreover, fewer years of education has been associated with a positive response to CT + Memory Support relative to more years of education [34]. We hypothesize that all of these poorer response groups may derive special benefit from the Memory Support Intervention. Hence, while we expect all patients to benefit from the Memory Support Intervention, we have planned analyses to determine if these subgroups stand to gain the greatest advantage from experimental facilitation of memory for treatment. Second, there is evidence that improved mood in MDD is associated with improved declarative memory [51], although remitted MDD patients still exhibit significant memory deficits [23]. We have planned analyses to address this potential confound.

Over a 4-year period, adults with MDD (*n* = 178, including 20% for attrition) will be randomly allocated to CT + Memory Support or CT-as-usual and will be assessed at baseline, post treatment and at 6 and 12 months’ follow-up (6FU and 12FU). The first aim is to assess whether the Memory Support Intervention (1) improves the course of illness and (2) reduces functional impairment. Compared to those receiving CT-as-usual, we expect that patients receiving CT + Memory Support will experience greater symptom reduction on measures of course of illness, as defined by the American College of Neuropsychopharmacology (ACNP) Task Force criteria, and on measures of functional impairment. The second aim is to evaluate whether patient memory for treatment mediates the relationship between treatment condition and outcome. Relative to CT-as-usual, we expect CT + Memory Support to be associated with better treatment outcome, and will be mediated by better patient memory for treatment, measured by the Patient Treatment Recall Task. The third aim is to evaluate if previously reported poor treatment response subgroups moderate target engagement. We expect that the relationship between memory support dose and outcome will be positive and stronger among those who are older, have lower IQ, have more chronic depression, have poorer baseline declarative memory performance and have fewer years of education.

## Method/design

### Study design and setting

This is a prospective randomized controlled study. Adults (*n* = 178) who meet criteria for MDD will be randomly assigned, in a 1:1 parallel group design, to CT + Memory Support or CT-as-usual (see Fig. 1 for a flow chart of the study design). Randomization is stratified by age (≤49, 50 + years) and depression chronicity (< 2 years, ≥ 2 years) [46]. Participants receive a battery of outcome measures pre-treatment and post-treatment (i.e., within 2 weeks after the final treatment session) and at 6 and 12 months’ follow-up. Additional assessments of patient and therapist memory for treatment take place in weeks 4, 8, 12 and 16 of treatment for the mediation analysis.

**Fig. 1 Fig1:**
[figure not shown]
Standard Protocol Items: Anticipated patient flow for the randomized clinical trial

The assessment team is blind to treatment allocation. Randomization will be conducted using a computerized, random-number generator where the planned stratified randomization is a part of the generation of the allocation sequence. Only the project coordinators in charge of randomization and of the Memory Support Rating Scale (MSRS) scoring know the treatment allocation of each participant. A Data Safety and Monitoring Board (DSMB) will review the study every 6 months during the active treatment phase. The Standard Protocol Items: Recommendations for Interventional Trials (SPIRIT 2013) Checklist (see Additional file 1) and Figure (see Fig. 2 Standard Protocol Item: Recommendation for Interventional Trials diagram) are provided [52].

**Fig. 2 Fig2:**
[figure not shown]
Standard Protocol Items: SPIRIT Figure: Schedule of enrollment, interventions, and assessments

For participants who discontinue, the assessment team will endeavor to collect all assessment data, prioritizing the primary outcomes.

### Participants

A total of 178 adults who meet the criteria will be recruited. Recruitment will be conducted in the Bay Area, CA, United States by clinician referral and advertisements. Eligibility is assessed first by a phone interview and then, if the individual is eligible after the phone interview, a more detailed, in-person interview. To enhance representativeness and generalizability, the inclusion and exclusion criteria are kept to a minimum.

### Inclusion criteria

The inclusion criteria are:Age 18 + yearsWilling and able to give consent. Participants must consent to being video-recorded (necessary for MSRS scoring) and to NIMH data sharing^1^
English language fluencyDiagnosis of major depressive disorder (MDD), first episode, recurrent or chronic according to the *Diagnostic and Statistical Manual of Mental Disorders, Fifth Edition* (DSM-5)Minimum score 26 or above on the Inventory of Depressive Symptomatology, Self-Report (IDS-SR). This cutoff denotes at least “moderate” depressionIf taking medications for mood, medications must be stable for the past 4 weeks

### Exclusion criteria

The exclusion criteria are:History of bipolar disorderHistory of psychosis or psychotic featuresLifetime history of failure to respond to four or more sessions of CBT/CT for depressionCurrent non-psychotic disorder if it constitutes the principal diagnosis and if it requires treatment other than that offered in the project. “Principal” is defined as the disorder currently most distressing and disabling, using a widely accepted severity rating scale capturing distress and interference (0–8, 4 + indicates clinical severity)Moderate or severe substance use in the past 6 months where “moderate” is defined as 4–5 symptoms and “severe” is defined as 6 + symptoms of those listed in DSM-5 for each of the substance-related disordersEvidence of any medical disorder or condition that could cause depression, preclude participation in CT, or is associated with memory problems, that is not currently stabilized and/or managed under the care of a physician or the presence of an active and progressive physical illness or neurological degenerative diseaseCurrent suicide risk sufficient to preclude treatment on an outpatient basis (assessed by the Columbia-Suicide Severity Rating Scale) or current homicide risk (assessed by our staff or referring treatment provider)Pregnancy or breastfeedingNot able/willing to participate in and/or complete the pre-treatment assessments

Excluding participants whose medications need to be changed is neither feasible nor representative of clinical practice [53]. Strategies to manage potential medication confounds are: (1) medications must be at stable doses for 4 weeks prior to randomization and (2) medication use and changes, along with participation in other treatments/therapy, will be recorded. All medication decisions will ultimately rest with the treating physician and participant.

Following the precedent set in prior research [54], participants with a lifetime history of failure to respond to four or more sessions of CBT for depression will be excluded. Participants who have engaged in moderate or severe substance use in the past 6 months will also be excluded. “Moderate” substance use is defined as four to five symptoms and “severe” substance use is defined as six or more of the symptoms listed in the DSM-5 for each of the substance-related disorders.

### Measures

The primary and secondary outcomes are presented in Additional file 2. Additional file 3 lists all of the measures as well as the timing for administration. Except where specified in Additional file 3, the measures described below will be delivered at each assessment point.

In addition to demographics (age, contact information, gender, race/ethnicity, family, education, employment, living arrangements, government assistance, housing) and assessment of medical history the following measures will be administered:

#### Diagnostic

To evaluate current and past psychiatric disorders the *Structured Clinical Interview for DSM-5 (SCID)* [55, 56] will be administered along with the *Longitudinal Interval Follow-up Evaluation (LIFE)* [57] to further ascertain presence/absence of MDD, number and length of mood episodes and remission, response, relapse, recovery, recurrence and time to relapse or recurrence (see Additional file 1 for definitions which are drawn from the ACNP criteria [58]).

#### Symptomatic

The *IDS-SR* [59], a widely used self-report measure of depression severity, as well as two subscales (ideation and behavior) from the lifetime and current version of the Columbia-Suicide Severity Rating Scale (C-SSRS) [60–62], will be administered. The *Quick Inventory for Depression Symptomatology* (QIDS) is administered every treatment session [38] for clinical purposes (monitoring of suicide and depression symptoms).

#### Functional impairment

The *World Health Organization Disability Assessment Schedule 2.0 (WHODAS 2.0)* [39] as well as the four-question *“Healthy Days”* (CDC HRQOL-4) core module developed by the CDC [63] will be administered.

#### IQ

The *National Adult Reading Test (NART)* [64] estimates premorbid intelligence. The total number of errors are calculated and used to derive an estimate of full-scale IQ and verbal IQ.

#### Memory

The *Patient Treatment Recall Task* [10] and the *Generalization Task* [65] are included as early indicators of target engagement and the trajectory of recall and learning over time. *Classical tests of memory* include a test of declarative memory—the *Episodic Face-Name Learning Task* [66–68]—which is the domain in which the most profound declines in MDD are observed [69–74]. Working memory will be assessed via the *N-Back* [75] because working memory aids the formation and retention of long-term declarative memories via attentive and elaborative-rehearsal processes [76, 77].

#### Memory Support Rating Scale (MSRS) [78]

Selected treatment session video-recordings will be coded using the *MSRS* to establish the dose of memory support delivered.

*Medication and other treatment tracking logs* will be used to record the additional treatments patients are receiving and any changes in those treatments throughout the duration of the study.

*Treatment credibility/expectancy* is administered at session 2, post-treatment, 6FU and 12FU via the *Credibility/Expectancy Questionnaire* [79, 80].

#### Exploratory measures

As this is a relatively new program of research and we wish to learn as much as possible, we have included the following measures on a pilot/exploratory basis: *Patient Usefulness and Utilization of Cognitive Therapy Skills Scale* (delivered post treatment, 6FU and 12FU), the *Competencies in Cognitive Therapy Scale* [81] (delivered at post treatment, 6FU and 12FU), *Patient Conceptualization of Depression Task* (delivered at the pre-treatment assessment, post treatment and 6FU) and a *Memory Support Treatment Provider Checklist* to be completed by the therapists delivering CT + Memory Support (delivered during weeks 4, 8, 12 and 16 of the treatment).

### Treatments

Both treatments are comprised of 20–26 × 50-min sessions conducted over 16 weeks.

#### CT-as-usual

CT was developed by Beck et al. [82] and has incorporated a number of innovations [83, 84]. Treatment maneuvers are designed to identify, reality test, and correct distorted beliefs and information processing [82]. CT for MDD will be conducted according to the standard manuals [82, 85, 86].

#### CT + Memory Support

The Memory Support Intervention is a manualized adjunctive treatment that will be delivered alongside CT-as-usual. The Memory Support Intervention is designed to improve patient memory for treatment. Distilled from the cognitive science and education literature based on carefully honed criteria [18], the Memory Support Intervention is comprised of eight memory-promoting strategies: attention recruitment, categorization, evaluation, application, repetition, practice remembering, cue-based reminder and praise recall. These strategies are proactively, strategically and intensively integrated into treatment-as-usual to support encoding. Memory support is delivered alongside each “treatment point,” defined as a main idea, principle, or experience that the treatment provider wants the patient to remember or implement as part of the treatment [10]. We acknowledge that some memory support is a standard part of certain treatments, including CBT [84, 87]. In the present study, the two treatment arms will differ in the “dose” of memory support. An underpowered pilot study indicated that the Memory Support Intervention effectively increases the amount of memory support delivered and improves depression outcome on certain measures [34].

#### Intervention fidelity

Treatment session video-recordings that occur at session 2 and at weeks 4, 8, 12 and 16 are coded using the MSRS [78] to establish the dose of memory support delivered. CT + Memory Support therapists are blind to which sessions are coded. CT-as-usual therapists are blind to the memory support portion of the research.

To reduce expectations impacting the delivery of each arm and to ensure purity of delivery [88], each treatment provider will be allocated to deliver only one of the two treatments. The rationale is that therapists report that once they have mastered memory support it is difficult to deliver CT-as-usual.

Clinicians use a treatment manual and receive weekly supervision to standardize treatment administration. Treatment sessions are video- and audio-taped and a random selection are rated using the *Cognitive Therapy Rating Scale* [89] which is a measure of general intervention skills and CBT-specific skills. The goal of this intervention is to maintain consistency and ensure adherence to the protocols [89].

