### Data analysis

#### Preliminary data evaluation

Missing or aberrant data will be verified. Data will be audited for quality and completeness. Evaluation of distributions detects outliers and ensures that assumptions of planned analyses are met. Baseline differences between groups will be examined (e.g., IQ, demographics, psychiatric and medical comorbidity, medications). Statistical tests will not be used to select covariates in the primary intent-to-treat analysis [90–92]. Instead, the potential influences of baseline differences will be evaluated as moderators. If remedial training is given to a therapist whose adherence to the treatment protocol is not satisfactory, this will be included as a dummy-coded covariate in all analyses.

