#### Missing data

Longitudinal analyses will use all available data and produce valid inferences if attrition depends on treatment group or on previous outcomes for the same participant [95]. If dropout is associated with other variables, they will be added as predictors to reduce bias due to data missing not at random.

#### Hypothesis 1

*CT + Memory Support will be superior to CT-as-usual for improving course of illness and reducing functional impairment at post-treatment, 6FU and 12FU on primary outcomes* listed in Additional file 1. Treatment groups will be compared on categorical outcomes (e.g., remission, relapse) using logistic regression to evaluate the odds of remission at post-treatment, and the odds of relapse at 6FU and 12FU. For the continuous variables (e.g., IDS-SR), we will test for differences in the mean trajectories across time between CT + Memory Support and CT-as-usual using Hierarchical Linear Modeling (HLM) [96–98]. The 1st level will represent within-person variation, and will include time indicators (or dummy variables) as predictors (post-treatment, 6FU and 12FU, with baseline as reference). The 2nd level represents between-person variation in the intercept and coefficients of the time indicators, and will include a dummy variable for arm (CT + Memory Support vs. CT-as-usual) as the predictor variable. Interactions between arm and the time indicators will be retained only if found to be significant at the 5% level using likelihood-ratio tests. Significant interaction terms between arm and time indicator suggest that there are different trajectories across time and between arms, and will be graphed to interpret the interaction.

#### Hypothesis 2

*Relative to CT-as-usual, the relationship between CT + Memory Support and better treatment outcome will be mediated by patient memory for treatment*. Outcome will be measured by IDS-SR at post-treatment, 6FU and 12FU. Patient memory will be measured by the Patient Treatment Recall Task and the Generalization Task at weeks 4, 8, 12 and 16 of treatment. A mediation model will be specified using Structural Equation Modeling [99]. Indirect effects from CT + Memory Support to better treatment outcome via patient memory will be assessed.

#### Hypothesis 3

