#### Intervention fidelity check

MSRS scores will be compared for CT + Memory Support vs. CT-as-usual via independent samples *t* tests. To test the assumption that memory for CT session content improves as a result of CT + Memory Support we will use HLMs to analyze differences in linear rates of change between the two groups on the Patient Treatment Recall Task and Generalization Task delivered during weeks 4, 8, 12 and 16 of the treatment phase and at 6FU and 12FU.

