#### Power analysis

Based on the pilot study [34], using Glimmpse [104, 105] for repeated measures design, we took into account the four repeated measurements (pre-treatment, post-treatment, 6FU, 12FU). At an alpha level of 0.05 with 80% power, the sample size is estimated to be 80 for the IDS-SR. We also used G*Power and the Demidenko [106] method to calculate estimated sample size for binary mood outcomes (i.e., remission, relapse). The sample sizes are estimated to be 103 (remission) and 118 (relapse). Finally, Fritz and MacKinnon [107] provide recommendations for mediation sample size, and estimates from pilot data indicate that the recommended sample size is 148. Adding an additional 20% for possible attrition, we propose a sample of 178.

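### Each therapist delivers only one arm, but the stated models and sample sizes make no allowance for therapist clustering; if therapists differ, type I error exceeds 5% and power for relapse and remission is most exposed

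*Protocol article*

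**What the plan says.** - **Delivery.** Intervention fidelity: "each treatment provider will be allocated to deliver only one of the two treatments". The reason given is that therapists who have mastered memory support report difficulty in going back to usual CT. Patients are randomized individually, 1:1.
- **Continuous outcomes.** Data analysis, Hypothesis 1, writes the HLM out level by level: "The 1st level will represent within-person variation", and "The 2nd level represents between-person variation in the intercept and coefficients of the time indicators". Arm enters as a predictor at the second level. Baseline is the reference time point. No level stands above the patient.
- **Binary and time-to-event outcomes.** Groups are compared "using logistic regression to evaluate the odds of remission at post-treatment, and the odds of relapse at 6FU and 12FU". Additional planned analyses adds Cox regression for time to relapse. Neither names a therapist term.
- **Fidelity check.** "MSRS scores will be compared for CT + Memory Support vs. CT-as-usual via independent samples" t tests.
- **The only therapist-related term.** Preliminary data evaluation provides a dummy covariate that applies "If remedial training is given to a therapist whose adherence to the treatment protocol is not satisfactory". It is conditional and does not represent clustering.
- **Sample size.** Power analysis says "we took into account the four repeated measurements (pre-treatment, post-treatment, 6FU, 12FU") and names no other source of correlation. It then says "At an alpha level of 0.05 with 80% power, the sample size is estimated to be 80 for the IDS-SR", followed by 103 for remission, 118 for relapse and 148 for mediation. Adding 20% to the last gives 178.

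**The concern.** When no therapist works in both arms, the difference between arms contains the difference between two sets of therapists. Randomizing patients does not remove that component, and adding patients per therapist does not average it away; only more therapists do. A model that treats patients as independent leaves it out of the standard error. A few unusually effective or ineffective therapists in one arm could then be read as an effect of Memory Support, in a trial that its Discussion presents as confirmatory and definitive.

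The same omission in the sample size means that each stated N buys less information than assumed. The MSRS comparison is the plainest case, because the scale scores what the therapist does. Patients of one therapist are repeated observations of one person's behaviour.

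**Working it through.** **What can be reproduced.** The article gives no effect size, standard deviation, event rate or within-person correlation, so 80, 103, 118 and 148 cannot be re-derived. The last step can: 148 × 1.2 = 177.6, rounded to 178. After a 20% loss, 178 × 0.8 = 142 patients remain.

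**Inputs**
- From the article: alpha 0.05; N = 80, 103, 118, 148; 142 analysable, as above.
- Assumed, because not stated: two-sided tests; m = 9 patients per therapist (142 / 9, about 16 therapists); therapist ICC of 0.02, 0.05 or 0.10.
- Assumed: 103 and 118 correspond to 80% power. The text attaches 80% in words only to the IDS-SR figure.

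**Formulas**
- Design effect: DE = 1 + (m − 1) × ICC
- Effective N = 142 / DE
- Real type I error of an unadjusted 5% test = 2 × [1 − Φ(1.96 / √DE)]
- Power = Φ(2.8016 × √(effective N / N80) − 1.96), where N80 is the size taken to give 80%

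**Results (normal approximation)**

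| ICC | DE | Effective N | Type I error | IDS-SR | Remission | Relapse |
|---|---|---|---|---|---|---|
| 0 | 1.00 | 142 | 5.0% | 96% | 91% | 87% |
| 0.02 | 1.16 | 122 | 6.9% | 93% | 86% | 81% |
| 0.05 | 1.40 | 101 | 9.8% | 88% | 79% | 74% |
| 0.10 | 1.80 | 79 | 14.4% | 79% | 69% | 63% |

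**Break-even.** Power falls to 80% when DE = 142 / N80: 1.78 for IDS-SR, 1.38 for remission and 1.20 for relapse. At m = 9 the corresponding ICCs, (DE − 1) / 8, are about 0.097, 0.047 and 0.025. For mediation, 142 is already below 148 before any clustering.

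**Sensitivity**
- With 15 per therapist and ICC 0.05, DE = 1.70 and power is 82% / 71% / 65% (IDS-SR / remission / relapse).
- With a t reference on therapists minus 2 degrees of freedom (16 therapists, 142 patients), power is 90% / 81% / 76% at ICC 0.02, 84% / 74% / 68% at 0.05 and 74% / 63% / 57% at 0.10.
- With 148 evaluable, type I error runs from 5.6% (24 therapists, ICC 0.01) to 23.7% (8 therapists, ICC 0.10).

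**Which ICC matters in the HLM.** Baseline is an outcome time point, and the treatment effect is read from the arm-by-time terms. Therapists can affect outcomes only after baseline. A therapist intercept that is constant over time adds the same quantity to baseline and to follow-up, so it largely cancels from the change. The relevant ICC is that of the change from baseline, and therapist variation has to sit on the post-baseline time coefficients. A simulation agrees: with 16 therapists and a post-baseline ICC of 0.10, ignoring therapist in the change score gave about 14.5% type I error, and a therapist-level analysis restored 5%.

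**The case against.** Several points can fairly be made for the plan.

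- **The trial is larger than its main outcome needs.** A reader might infer from the missing design effect that 80% power is not delivered. The figures do not support that as a general statement. The trial is sized on the mediation N of 148, not on 80. At ICC 0.02 all three outcomes stay above 80% on the normal approximation, and IDS-SR does so up to an ICC of about 0.10. This objection stands, and the power point must be made outcome by outcome.
- **The ICC is unknown.** A reader might also infer that type I error certainly exceeds 5%. That holds only if the therapist ICC is above zero, and the document gives no value. Manuals, weekly supervision and rated recordings aim at uniform delivery and may keep it small. They do not make it zero by design, and no stated rule checks it.
- **A condensed article leaves detail to the analysis plan.** For the logistic, Cox and mediation models this has force, since only the model family is named. It does not rescue the HLM, whose levels are spelled out, or the MSRS comparison, whose test is named.
- **The MSRS test is a fidelity check, not a primary hypothesis.** True, so its consequences are smaller. No figure in the document says how strong the therapist correlation of MSRS scores is; the argument rests on what the scale measures.

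**Conclusion.** The point holds in conditional form. The delivery rule nests therapists in arm, while the written HLM and the MSRS t tests treat patients as independent. This is a stated rule that does not fit the design, not an omitted detail. If therapists differ, standard errors are too small by √DE. For 9 patients per therapist and ICC 0.02 to 0.10 that is a factor of 1.08 to 1.34, with a real type I error of 6.9% to 14.4%. These sizes rest wholly on an assumed ICC and caseload.

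On power, the sample sizes contain no allowance for clustering, but the consequence differs by outcome. IDS-SR has a real reserve, remission a modest one, relapse a thin one and mediation none. The remission and relapse figures also rest on reading 103 and 118 as 80% sizes. The normal approximation flatters all of them compared with therapist-based degrees of freedom. Type I error is the more serious consequence, because the surplus of patients does nothing to correct it.

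**What to change.** - In the HLM, add therapist, nested in arm, as a third level with random effects on the post-baseline time coefficients. A common therapist intercept alone would leave most of the inflation in place.
- In the logistic, Cox, mediation and MSRS comparisons, use a therapist random effect or cluster-robust standard errors with a small-sample correction.
- Base degrees of freedom on the number of therapists (Satterthwaite or Kenward-Roger where the model allows).
- State the number of therapists per arm, and restate power for each outcome at the planned N over a stated ICC range, with the power level behind 103 and 118 made explicit.

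The cost is mainly wording in the analysis section, plus recording which therapist treated each patient if that is not already done. The design need not change. Confidence intervals will widen and the stated power will look less favourable, most of all if there are few therapists.
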